#### Handling of missing data

We will use an electronic case report form (eCRF) with a pragmatic design and incentive strategies to maximise complete registration to minimise the occurrence of missing data. If less than 5% of the data are missing on any primary or secondary outcome, a complete case analysis without input of missing values will be performed. If missing data are more than 5%, a blinded statistician will assess whether data are ‘missing completely at random’ based on a rational assessment of the pattern of missing data. If it is concluded that data are not ‘missing completely at random’, multiple imputation using chained equations will be performed by creating at least ten input data sets under the assumption that the data are missing at random. If appropriate, we will also consider carrying out ‘best–worst’ and ‘worst-best’ analyses [32]. We will use outcomes and the most important baseline characteristics in the multiple imputations. The unadjusted, non-imputed analysis will also be made available.

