### Sample size and power justification

#### Sample size estimation

Data from the only previous randomised clinical trial suggest a VP-shunt implantation proportion of 63% in patients with acute need of CSF diversion following aSAH [5]. The mortality following aSAH is commonly quoted to be 27% to 50%, while 5.8% of patients develop an EVD-related infection [2, 7]. Assuming an incidence of either of the three components of the composite primary outcome (VP-shunt implantation, all-cause mortality, or EVD-related infection) within 6 months of 80%, an *α* = 0.05 (two-sided), and a *β* = 0.20, 2 × 122 participants are required to detect a 20% relative risk reduction or increase calculated using R (R Core Team, Vienna, Austria)*.* For composite outcomes, one missing component will result in missingness in the composite outcome. Number and percent missing due to a missing component will be stated in the report or in a diagram to avoid biased result, e.g. from death alone.

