### General analysis principles

Statistical analyses will be handled using the latest stable version of R (R Core Team, Vienna, Austria) and/or Stata (StataCop LLC, Texas, USA). The analyses will be carried out using the intention-to-treat principle where all randomised participants will be included in all analyses. The baseline characteristics will be presented for each group (Tables 2 and 3). The threshold for significance for all outcomes will be below 0.05, as the primary conclusions will be drawn based on the primary outcome [22]. All the remaining secondary and exploratory outcomes will be interpreted as hypothesis generating outcomes.

**Table 2 Tab2:** Baseline characteristics based on simulated data

	A	B
*n*	122	122
Age (mean (SD))	57.8 (0.90)	59.1 (0.50)
Gender, female (*n*, %)	85 (70.9)	90 (73.8)
Hypertension (*n*, %)	46 (37.2)	51 (41.3)
Aneurysm location (*n*, %)		
ICA	19 (15.6)	14 (11.5)
ACA/ACOM	50 (41)	56 (45.9)
MCA	16 (13.2)	11 (9.1)
Basilar artery	25 (20.5)	23 (18.9)
Vertebral artery/PICA	8 (6.3)	10 (8.2)
Pericallosa	4 (3.2)	2 (1.6)
Treatment modality		
Endovascular	50 (41)	56 (45.9)
Surgical	72 (59)	66 (54.1)
WFNS grade		
I	60 (49,2)	55 (45,1)
II	11 (9,0)	12 (9,8)
III	7 (5,7)	12 (9,8)
IV	29 (23,8)	24 (19,7)
V	15 (12,3)	19 (15,6)
Hunt Hess		
1–3	70 (57.4)	74 (60.6)
4–5	52 (42.6)	48 (39.4)
Glasgow Coma Score on admission		
15–14	42 (34.2)	46 (37.7)
13–9	21 (17.1)	17 (14.1)
8–3	58 (47.7)	55 (45.1)
Modified Fisher		
0–3	52 (42.8)	56 (45.9)
4	70 (57.2)	66 (54.1)
Modified LeRoux		
0–5	50 (41)	56 (45.9)
6–16	72 (59)	66 (54.1)
Nicotine use		
Current	21 (17.1)	18 (14.6)
Former	13 (10.4)	10 (8.2)
Never	88 (72.1)	94 (77.1)
Intubated at admission (*n*, %)	45 (36.9)	41 (33.6)
Acute hydrocephalus (*n*, %)	78 (63.9)	71 (59.1)

**Table 3 Tab3:** Summarised results of outcomes based on simulated data

	A	B	Estimate	*p*-value
*n*	122	122		
Primary outcome				
Composite outcome—*n* (%)	43 (35)	36 (30)	*RR (95%CI)* 1.01 (0.99 to 1.03)	0.05
Secondary outcomes				
SAE excl. mortality—median (IQR)	340	320	*median diff (95%CI)* 330 (329 to 349)	0.45
EQ-5D-5L -	60	56	*mean diff (95%CI)* 58 (55.1 to 59.2)	0.69
Fatigue Severity Scale	4.3	4.8	*mean diff (95%CI)* 4.5 (3.9 to 5.3)	0.05
Mean FSS (SD)	5.21 (1.8)	4.1 (1,4)	*mean diff (95%CI)* 4.6 (-4 to 14)	0.69
Clinical fatigue (FSS ≥ 4)	88 (72.3)	82 (67.2)	*mean diff (95%CI)* 3.4 (3.29 to 4.21)	0.34
Components of the primary outcome				

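### Above 5% missing data, multiple imputation depends on a finding that the data are not MCAR, with no criterion given, although observed data can contradict MCAR but never establish it

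*SAP article*

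**What the plan says.** All of the rule stands under Handling of missing data in the SAP article.

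- Below the threshold: "If less than 5% of the data are missing on any primary or secondary outcome, a complete case analysis without input of missing values" is to be run.
- Above it: "If missing data are more than 5%, a blinded statistician will assess whether data are" MCAR, and the basis for that is "based on a rational assessment of the pattern of missing data".
- If the conclusion is that data are not MCAR, chained-equations imputation follows, with ten or more imputed data sets and missingness at random (MAR) assumed. Outcomes and the most important baseline characteristics enter the imputation.
- If the conclusion is MCAR, no analysis is named.
- Best-worst and worst-best analyses are optional: "If appropriate, we will also consider carrying out" them.
- "The unadjusted, non-imputed analysis will also be made available". There is no matching promise that an imputed analysis will always be shown.

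Two other places bear on this. Sample size estimation says that "one missing component will result in missingness in the composite outcome". Sensitivity analyses lists per-protocol, time-origin and dichotomised analyses, but none for missing data.

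**The concern.** MCAR says that missingness is unrelated to anything, observed or unobserved. A pattern in the observed data (more missing in one arm, one site or one severity grade) can show that MCAR is false. The absence of a visible pattern cannot show that it is true: the sample may be too small to reveal it, or missingness may depend on the value that was not seen. The rule nevertheless needs a positive MCAR conclusion to leave imputation out, and gives the statistician no criterion for reaching it.

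The two possible errors are not equally costly. Imputing under MAR remains valid if data happen to be MCAR, at the price of some dependence on the imputation model. Not imputing when missingness follows measured severity can leave a selection effect that imputation could have reduced.

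The outcomes exposed are the primary composite and the secondary outcomes. EQ VAS and the Fatigue Severity Scale are collected at 6 months, and sicker participants may plausibly respond less often; that is an assumption, since the article does not discuss it. For the composite, losing one component makes the whole outcome missing, which makes it easier to cross 5%. The choice is made once the missing-data pattern is known, in a plan whose stated purpose is to limit data-driven interpretation.

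**Working it through.** **The plan's own figures.** The article gives no expected missing-data rate and no power for the MCAR assessment, so there is no figure to reproduce on this point. The sample size is not in dispute: 80% versus 64%, two-sided 5% and 80% power give 123 per group by the pooled-variance formula, and 122 per group gives 79.9% power. The threshold is 0.05 × 244 = 12.2 participants, so the rule starts at 13 missing.

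**Step 1. The branches side by side.**

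| Missing | Statistician's conclusion | Analysis in the plan |
|---|---|---|
| Under 5% | none needed | complete case |
| Over 5% | not MCAR | chained-equations imputation under MAR; non-imputed also shown |
| Over 5% | MCAR | not named; the only analysis left is the non-imputed one |

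The last row is an inference from what the text leaves open. It has no upper limit on the amount missing.

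**Step 2. How visible a real departure from MCAR would be (illustration).** Assumptions, none from the plan: one binary baseline factor splits 244 into 122 and 122; overall missingness *m* is 6% or 10%; the odds of missingness differ by a factor OR of 2 or 3; the pattern is judged by Fisher's exact test at 5%. The two missingness probabilities solve

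(p_low + p_high)/2 = m and [p_high/(1 − p_high)] / [p_low/(1 − p_low)] = OR.

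Power is the summed binomial probability of all 2 × 2 tables with p < 0.05.

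| m | OR | p_low | p_high | Expected missing | Fisher | Uncorrected chi-square |
|---|---|---|---|---|---|---|
| 10% | 2 | 0.070 | 0.130 | 8.5 vs 15.9 | 27% | 35% |
| 10% | 3 | 0.054 | 0.146 | 6.6 vs 17.8 | 60% | 69% |
| 6% | 2 | 0.041 | 0.079 | 5.0 vs 9.6 | 15% | 23% |
| 6% | 3 | 0.031 | 0.089 | 3.8 vs 10.8 | 36% | 47% |

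A doubling of the odds is missed more often than found under either test.

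**Step 3. What a missed pattern could cost.** At 10% missing and OR 2, the worse half makes up (1 − 0.1303) / [(1 − 0.1303) + (1 − 0.0697)] = 0.8697/1.8000 = 48.3% of those observed, instead of 50%. Assume a 20-point EQ VAS gap between the halves and selection in one arm only. The treatment difference then shifts by 20 × (0.500 − 0.483) ≈ 0.34 points. With OR 3 the share is 0.8539/1.8000 = 47.4% and the shift about 0.51. The planned difference is 11 (Power estimations), so the shift is about 3% to 5% of it. If selection is the same in both arms and there is no interaction, the shift is zero.

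**Step 4. What MAR imputation would not repair.** Take a true composite risk of 80% in both arms and 10% missing per arm. Let missingness be twice as frequent among events in one arm and twice as frequent among non-events in the other.

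- First arm: 0.10/(0.8 × 2 + 0.2) = 0.0556, so the observed risk is 0.8 × (1 − 0.1111)/0.9 = 0.790.
- Second arm: 0.10/(0.8 + 0.2 × 2) = 0.0833, so the observed risk is 0.8 × (1 − 0.0833)/0.9 = 0.815.
- Complete-case relative risk: 0.790/0.815 = 0.97 instead of 1.00.

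This missingness depends on the outcome itself, which an imputation under MAR is not built to correct. Best-worst analyses bound it. With 12 missing and 110 observed per arm and an observed relative risk of 0.80, events are 0.80 × 110 = 88 and 0.64 × 110 = 70.4. The bounds are 70.4/(88 + 12) = 0.70 and (70.4 + 12)/88 = 0.94.

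**The case against.** The strongest reply is that the plan prescribes a rational assessment, not a significance test. Such an assessment can weigh arm, site, several covariates, reasons for missingness and clinical knowledge. If the sickest participants are the ones missing, a sensible statistician would say so, and imputation would follow. This stands. A reader might infer from Step 2 that imputation would be skipped in about 73% or 85% of doubled-odds cases. The article does not support that: nowhere does it equate a non-significant pattern with MCAR.

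A second reply is that failing to see a pattern is not the same as bias. This also stands. Step 3 gives shifts of 0.3 to 0.5 points under assumptions that do not cancel across arms.

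Two further readings are tempting and do not hold.

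- *The MCAR step can do nothing but harm.* The planned linear and logistic models adjust for the stratification variables and site. A complete-case fit of such a model can be valid without MCAR if missingness depends only on those covariates. If MCAR is true, complete-case analysis is unbiased and needs no imputation model.
- *The rule contradicts the statement that "all randomised participants will be included in all analyses".* That is a general intention-to-treat principle. Other sections openly provide for missing data and report its percentage per group, and the change proposed here keeps complete-case analysis below 5%.

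There are safeguards: the assessor is blinded, two statisticians analyse independently, both reports are published, and secondary outcomes are called hypothesis generating. These make the choice visible and limit deliberate steering. They do not supply the missing criterion, and they do not guarantee that an imputed result is shown.

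**Conclusion.** The point holds as a badly fixed decision rule. Above 5% missing, the imputed analysis rests on one judgement with no stated criterion, and the judgement that removes it is one that observed data can never confirm. That the non-imputed analysis then becomes the main result is an inference, because the MCAR branch is left blank; the text offers no other candidate.

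Its numerical consequence is unknown and may be small. The detection probabilities of 27% and 15% rest on assumed missingness rates, an assumed odds ratio, a single binary factor and a test the plan does not prescribe. They show that a real pattern can easily go unnoticed in 244 participants, and no more than that. The document does not support a claim of large bias. The case for change is that the step protects little, the alternative is already specified, and the plan aims to remove this kind of discretion. It should be changed, but it does not undermine the trial.

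**What to change.** Delete the MCAR assessment and state, in substance: if more than 5% of data are missing on a primary or secondary outcome, the primary analysis of that outcome uses multiple imputation by chained equations, with arm, the stratification variables, site, baseline severity and the other outcomes in the imputation model; the complete-case analysis is a sensitivity analysis.

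Because imputation assumes MAR, also make the best-worst and worst-best analyses definite above 5%, and define what a best and a worst value mean for the outcomes that are not dichotomous.

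The change is a few sentences, made before the group codes are broken. The imputation method is already chosen and the non-imputed analysis already promised, so the cost is slightly more analysis work and reliance on an imputation model, with perhaps a little precision lost if data really are MCAR. It does not settle how participants who die before 6 months are handled for EQ VAS and fatigue, and it leaves the sample size at 2 × 122.

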**Methods:**

DRAIN (*Danish RAndomised Trial of External Ventricular Drainage Cessation IN Aneurysmal Subarachnoid Haemorrhage*) is an international multicentre randomised clinical trial comparing prompt closure versus gradual weaning of the EVD after aSAH. The primary outcome is a composite of VP-shunt implantation, all-cause mortality, or EVD-related infection. Secondary outcomes are serious adverse events excluding mortality and health-related quality of life (EQ-5D-5L). Exploratory outcomes are modified Rankin Scale, Fatigue Severity Scale, Glasgow Outcome Scale Extended, and length of stay in the neurointensive care unit and hospital. Outcome assessment will be performed 6 months after ictus. Based on the sample size calculation (event proportion 80% in the gradual weaning group, relative risk reduction 20%, alpha 5%, power 80%), 122 participants are required in each intervention group. Outcome assessment for the primary outcome, statistical analyses, and conclusion drawing will be blinded. Two independent statistical analyses and reports will be tracked using a version control system, and both will be published. Based on the final statistical report, the blinded steering group will formulate two abstracts.

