## Statistical reports

After completion of the trial, data will be analysed by two independent statisticians blinded to the intervention, where ‘A’ and ‘B’ refers to the two intervention groups. The two statisticians will independently analyse all data and present the results in two independent reports. The coordinating investigator, the two statisticians, and the steering committee will compare these reports and discrepancies will be discussed. If the results differ significantly with similar or even identical analysis across statistical software, we will interpret the results using the most conservative result.

The statistical report with consensus on the definitive analyses in the manuscript is being tracked using a version control system and both statistical reports will be left unchanged and be published as supplementary material. Any analyses performed after unblinding will not be included in the statistical report.

Based on the final statistical report, two blinded abstracts with conclusions will be drawn by the steering committee: one assuming ‘A’ is the experimental group and ‘B’ is the control group and one assuming the opposite. These abstracts will utilise the results from the blinded reports, and when the blinding is broken, the ‘correct’ abstract with conclusions will be chosen.

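### The floor of ten imputed data sets is low for a primary p-value judged at 0.05 and, on the natural reading, produced twice independently; raising it to 100 costs almost nothing

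*SAP article*

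**What the plan says.** Handling of missing data sets two conditions for imputation: more than 5% missing on a primary or secondary outcome, and a blinded judgement that the data are not missing completely at random. If both hold, "multiple imputation using chained equations will be performed by creating at least ten input data sets", using outcomes and the most important baseline characteristics. Below 5%, a complete case analysis is done. The unadjusted, non-imputed analysis is to be made available in any case.

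Statistical reports adds: "The two statisticians will independently analyse all data and present the results in two independent reports". The reports are compared and discrepancies discussed. If the results differ materially although the analyses are similar or identical, the more conservative one is used for interpretation. Both reports are published unchanged.

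General analysis principles states: "The threshold for significance for all outcomes will be below 0.05". The primary conclusions rest on the primary outcome. The article gives no seed, no rule linking the number of imputations to the missing fraction, and no statement on whether the two statisticians share one set of imputed data.

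**The concern.** A p-value pooled over a small number of imputed data sets has a random part of its own. Two people who fit the same imputation and analysis models to the same data, with different seeds or in different packages (the plan allows R and/or Stata), get different p-values. At ten imputations that difference can be large enough to carry a result near 0.05 across the threshold.

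Two things would then be at stake: some power, because the plan settles a split against significance, and the value of the dual analysis as a check, because simulation noise would appear in two published reports as if it were an analytic discrepancy. Missingness above 5% cannot be ruled out, since under Sample size estimation one missing component makes the composite missing.

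**Working it through.** **Inputs from the SAP article.** 122 per group ("122 participants are required in each intervention group"); 80% events in the gradual weaning group; a 20% relative reduction ("participants are required to detect a 20% relative risk reduction or increase"), so 0.80 × 80% = 64%; two-sided alpha 0.05; at least m = 10 imputations.

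**Assumptions.** The article gives no expected missing fraction; 6%, 10% and 20% are used here. The simulation imputes by arm only and pools an unadjusted log relative risk by Rubin's rules. It does not use the planned mixed-effects logistic model.

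**Step 1, the plan's own figure.** With the arcsine formula, h = 2·asin(√0.80) − 2·asin(√0.64) = 2.2143 − 1.8546 = 0.3597, and n = 2(1.960 + 0.842)²/0.3597² = 121.3, which rounds up to 122. The pooled normal formula gives 123, and the power at 122 is 79.9%. The stated sample size is reproduced.

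**Step 2, size of the noise.** With fraction of missing information FMI, the Monte Carlo SD of the pooled z is about √(FMI/m), and that of the difference between two separate runs is about √(2·FMI/m). In this setting FMI is about equal to the missing fraction. At 10% missing and m = 10 the two SDs are √(0.10/10) = 0.10 and √(0.20/10) = 0.141. At m = 100 they are 0.032 and 0.045.

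**Step 3, rough split rate.** The chance that two runs straddle 1.96 is about E|difference| × density of z at 1.96, that is √(2/π)·√(2·FMI/m) × φ(Φ⁻¹(power)). Using the simulated single-run power at m = 100 (77.3%, 74.8%, 70.0%):

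- 6% missing, m = 10: 0.0874 × 0.302 = 2.6%
- 10% missing, m = 10: 0.1128 × 0.319 = 3.6%
- 20% missing, m = 10: 0.1596 × 0.348 = 5.5%

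Dividing by √10 gives 0.8%, 1.1% and 1.8% at m = 100. The approximation ignores noise in the estimated between-imputation variance, so it should run low when much is missing.

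**Step 4, simulation with true rates 80% vs 64%.** *Both significant* is the outcome when a split is resolved conservatively.

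| Missing | m | Runs split at 0.05 | Power, one run | Power, both significant |
|---|---|---|---|---|
| 6% | 10 | 2.7% | 76.6% | 75.2% |
| 6% | 100 | 0.8% | 77.3% | 76.9% |
| 10% | 10 | 4.1% | 74.4% | 72.4% |
| 10% | 100 | 1.3% | 74.8% | 74.1% |
| 20% | 10 | 7.2% | 68.5% | 64.9% |
| 20% | 100 | 2.0% | 70.0% | 69.0% |

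A repeat under the same assumptions gave splits of 2.5%, 3.9% and 7.6% at m = 10, and 0.8%, 1.2% and 2.2% at m = 100. From the table, the power lost under the conservative rule at m = 10 rather than 100 is 76.9 − 75.2 = 1.7, 74.1 − 72.4 = 1.7 and 69.0 − 64.9 = 4.1 points. Allowing for simulation error across runs, that is about 1, 2 and 4 points. For a single run the loss is small, about 0.3 to 1.6 points across runs.

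**Step 5, type I error (80% vs 80%, m = 10).** At 10% missing one run rejects in 4.6% of trials and both runs in 3.9%. At 20% the figures are 4.6% and 3.5%. Two runs split in 1.3% and 2.2%.

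**Step 6, where it matters.** The limiting p is the value with unlimited imputations.

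- 6% missing, m = 10: a limiting p of 0.053 gives a 95% Monte Carlo range of 0.038 to 0.076 and 44% splits; at 0.028 splits are 0.4%, and at 0.097 they are 0%.
- 10% missing, m = 10: a limiting p of 0.049 gives 0.031 to 0.081 and 50% splits; at 0.018 splits are 0%.
- 20% missing, limiting p of 0.041: m = 10 gives 0.019 to 0.089 and 45% splits; m = 100 gives 0.032 to 0.052 and 9%.

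**The case against.** Several points on the other side stand.

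- Ten is a minimum. A run with 50 or 100 already complies, so the plan does not commit to ten. What remains is that a primary result at ten complies equally.
- Imputation needs the judgement on the missingness mechanism as well as more than 5% missing, so the situation may never arise.
- Separate imputation is inferred. The plan says that the statisticians analyse all data independently and foresees differences between software packages, which makes it the natural reading, but nothing rules out a shared imputed set.
- The plan has a rule for split results, and it works against significance. The non-imputed analysis is also made available.
- The missing fractions are assumed. The planned imputation uses outcomes and baseline characteristics, so informative predictors would lower the missing information and every rate above.

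A reader might infer more: that the primary decision hangs on the random seed in general, or that false positives increase. The documents do not support either. Away from 0.05 the two runs agree, as Step 6 shows. Counting a trial as significant if either run was would reject in 3.9 + 1.3 = 5.2% of null trials at 10% missing, but the conservative rule excludes that choice. Nor should the fall in power from 80% be blamed on m: at 20% missing, one run with 100 imputations still has only about 70%, and that loss comes from the missing data.

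**Conclusion.** The point holds as a minor one. If imputation is triggered, run at the floor and drawn separately, identical analyses disagree at 0.05 in about 2.5%, 4% and 7.5% of trials at 6%, 10% and 20% missing. With 100 imputations this falls to about 0.8%, 1.2% and 2%. Under the conservative rule the floor costs about 1, 2 and 4 points of power, with no inflation of type I error.

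These figures rest on the design rates of 80% and 64%, on assumed missing fractions and on a simplified imputation model that probably overstates the effect. Precision and reproducibility are at issue, not validity. More imputations reduce the problem without abolishing it: at 10% missing, a limiting p of 0.049 still splits in 49% of pairs with m = 100.

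**What to change.** In Handling of missing data, raise the minimum from ten imputed data sets to 100, and state that the seed will be recorded. This needs one sentence and minutes of computing.

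Optionally, have both statisticians also analyse one common archived imputed set, or compare their results against it, so that simulation noise is not reported as an analytic discrepancy. If the common set replaces separate imputation, that step is no longer fully duplicated, which gives up part of what the two independent reports are meant to provide. The second statistician could check the imputation code instead. The higher floor is worth adopting whether or not this option is taken.
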